### 6.3 Treatment Incentive (Intervention Arm)

Participants in the incentive arm will be told that incentive payments will be made based on their study viral load measurements at pre-defined time points (6 weeks, 3 months and 6 months post-randomization). The 6 week incentive will be provided if the participant’s plasma HIV RNA level is either  $<400$  copies/mL (if baseline HIV RNA is undetectable), or if the level has had more than a  $2 \log_{10}$  drop compared to the baseline HIV RNA measurement (if baseline HIV RNA is detectable). Incentives at 3 and 6 months will be provided only if a participant’s plasma HIV RNA is  $<400$  copies/mL. Study staff will make incentive payments to participants once HIV RNA results that meet the pre-specified cut-off are received. The incentive strategy will be clearly explained verbally and on a printed voucher that is given to them.

The incentives will increase in value when participants are found to meet the pre-specified virologic suppression criteria at 6 weeks, 3 months and 6 months: i) a small, fixed incentive of about US\$5 for HIV

virologic suppression within a period of 6 weeks after the HIV test and; ii) an *additional amount* of about US\$10 at 3 months, and about \$15 at 6 months, if they continue to meet the criteria for virologic suppression (i.e. about US\$30 total if HIV virologic suppression is achieved and maintained throughout the 6 months period following randomization). If a participant in the incentive arm does not meet a pre-specified viral load threshold at any time point, no incentive will be given at that timepoint. If the virologic threshold for an incentive is missed at the 6 week or 3 month time-point, the subsequent incentive for an undetectable HIV viral load will be reset to the initial incentive value (up to \$5). In this way, the incentive increases in value over time for maintaining virologic suppression – thereby helping maintain the motivation to continue on ART -- and resets to a baseline lower value for missing an HIV virologic threshold.

#### 6.4 Standard of Care - No Incentive (Control Arm)

Participant will be offered standard adherence counseling and an unconditional cash transfer of up to US\$5 in order to promote linkage to care.

#### 6.5 Outcomes Measurement

##### 6.5.1 HIV Virologic Suppression

Primary outcome: The proportion of adults with plasma HIV RNA <400 copies/mL six months after randomization.

Secondary outcomes: 1) The proportion of adults with plasma HIV RNA <400 copies/mL 12 months after trial randomization; 2) Mean time to HIV RNA <400 copies/mL; 3) linkage to care within 3 months.

Predictors and mediators: Participants' socio-economic characteristics will be recorded at the time of the HIV test. We will also elicit participants' *time preferences* among those participants who did not participate in the HIV Testing Incentives Trial but who enroll in the Treatment Incentives Trial.

Schedule of measurements: All participants will have HIV RNA measured by phlebotomy (venipuncture) at the following time points: i) enrollment, ii) 6 weeks post-randomization; iii) 12 weeks post-randomization; iv) 24 weeks post-randomization; v) 48 weeks post-randomization. Participants who do not attend a clinic visit for phlebotomy during follow-up time points (6, 12, 24 and 48 weeks post-randomization) will be contacted to meet at a place of their choosing, or tracked in the community if they cannot be contacted by phone.

##### 6.5.2 Qualitative Measures

In-depth semi-structured interviews: We will recruit a random sample of participants who do and do not achieve HIV virologic suppression at 6 months post-randomization from each study arm for in-depth semi-structured interviews. These interviews will seek to understand *mechanisms* through which incentives succeeded or failed, and *characteristics* of adults who did achieve virologic suppression due to the treatment incentive. We will use the same approach to sampling described in the HIV Testing Incentives Trial (Section 5.6.2), and randomly select participants from each of the following groups.

Incentive group: i) About 10-20 adults who achieved the virologic suppression threshold at 6 weeks; ii) About 10-20 adults who achieve HIV RNA <400 copies/mL at 6 months; iii) About 5-10 adults who have detectable HIV RNA measures at 6 months;

No incentive (control) group: iv) About 10-20 adults who achieve HIV RNA <400 copies/mL at 6 months; and v) About 5-10 adults who have detectable HIV RNA measures at 6 months.

The interview guide will elicit participants' perceptions, attitudes and preferences related to incentives, and psychosocial and contextual factors that influence participants' responses to these incentives and the decision whether or not to take antiretroviral therapy.

#### 6.6 Data Management & Statistical Considerations

##### 6.6.1 Data Collection & Management

Staff will record all HIV RNA measures and study questionnaire data under each participant's study identification number (ID) in either paper lab logs, or password-protected study computers. Data from these logs or devices will be entered and transferred via a secure electronic transfer to our data center facility in Kampala and stored on a secure server.

### 6.6.2 Analysis

Primary analysis: We will compare the proportion of participants with HIV RNA <400 copies/mL between the two interventions using 2-tailed  $\chi^2$  analysis, or other appropriate statistical methods. Our *hypothesis* is that a higher proportion of those offered an incentive will achieve HIV RNA <400 copies/mL than those offered no incentive (the standard of care).

Secondary analysis: Using logistic regression analysis that adjusts for SES, or other appropriate statistical analyses, we will evaluate the impact of *time preferences* (discount rates) on the intervention's effectiveness, using an interaction term between preferences and intervention group. We *hypothesize* that participants with high discount rates (i.e., they discount future benefits heavily and focus on present benefits) are more likely to respond to the incentive than participants with low discount rates.

Qualitative analysis: Data collection and analyses will be similar to those described in Section 5.7.2.

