### 4. Study Design

a. HIV Testing Incentives Trial (Aim 1): Randomized, controlled trial (RCT) of three types of incentive strategies (lottery-based, loss aversion-based, and fixed incentives) and multiple incentive amounts among adult male residents of rural Ugandan study communities. Eligible men will be randomized in an equal ratio to study groups.

b. HIV Treatment Incentives Trial (Aim 2): Randomized, controlled trial of a financial incentive strategy (with escalating incentive amounts for early treatment initiation and treatment maintenance vs. the no incentive standard of care) on the primary outcome of HIV virologic suppression (plasma HIV RNA  $<400$  copies/mL 6 months after randomization) among HIV-infected adult residents of rural Ugandan study communities. Eligible adults will be randomized in a 1:1 ratio.

c. Repeat HIV Testing Incentives (Aim 3 Pilot Trial): Randomized, controlled pilot trial of loss aversion vs. gain-framed incentive strategies vs. no incentive for the primary outcome of acceptability and feasibility of participation in a loss aversion strategy, to promote repeat HIV testing among HIV-negative, high-risk residents of rural Ugandan study communities. Eligible adults will be randomized to a control group, a gain-framed incentive group, or loss-aversion based group in a 1:1:3 ratio.

d. Repeat HIV Testing Incentives (Aim 3 Trial): Randomized, controlled trial of loss aversion (deposit contract) vs. gain-framed incentive strategies vs. no incentive (control) for the primary outcome of retesting for HIV 3- and 6-months following enrollment among HIV-negative, high-risk adults recruited from study sites in southwestern Uganda. Eligible adults will be randomized to the three groups (control, gain-framed and loss aversion incentive groups) in a 1:1:1 ratio.

e. Sustainability and Cost-Effectiveness (Aim 4):

- i. *Sustainability of incentives on HIV testing behavior*: Prospective study of HIV testing uptake at community HIV testing venues up to four years after HIV Testing Incentives RCT participants took part in the RCT.
- ii. *Cost-effectiveness*: We will measure the full resources and associated costs of implementing the incentive interventions for HIV testing using micro-costing (to quantify resources used and unit costs), and time and motion logs of study staff.

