#### 6.1.3 Screening for Enrollment

##### 6.1.3.1 Inclusion Criteria

- (a) Aged  $\geq 18$  years;
- (b) Reside in one of the four selected study communities;
- (c) Positive result obtained from rapid HIV antibody test algorithm

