### 6.6.3 Sample Size & Accrual

Based on data from our pilot studies in Uganda, we anticipate that a minimum of 50% of participants will have HIV RNA <400 copies/mL by six months post-randomization in the control arm. With a sample size of approximately 400 adults, we have >80% power ( $\alpha=0.05$ , 2-sided) to detect a difference of at least 15% in HIV virologic suppression with the incentive intervention.

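### Aim 2 collects HIV RNA at enrollment, but the named primary test does not use it and the mean-time secondary has no rule for participants never suppressed; the cost is precision and clarity, not validity

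*Protocol*

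**What the plan says.** **Who enters.** Section 6.1.3.1 asks for adult age, residence and "Positive result obtained from rapid HIV antibody test algorithm". There is no viral-load or treatment criterion, and the only exclusion in Section 6.1.3.2 is an intention to move. The synopsis (Section 1.1) speaks of reaching or keeping an undetectable viral load. Section 6.3 has a separate 6-week rule for participants undetectable at baseline. Entrants who are already suppressed are therefore both eligible and expected.

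**What is measured.** Section 6.5.1: "All participants will have HIV RNA measured by phlebotomy (venipuncture) at the following time points: i) enrollment", then at 6, 12, 24 and 48 weeks.

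**Primary analysis.** Section 6.6.2: "We will compare the proportion of participants with HIV RNA <400 copies/mL between the two interventions", using a two-sided chi-square test, with room left for another suitable method. Enrollment HIV RNA is not named as a covariate or stratum. The only adjustment named for Aim 2 is socio-economic status, in the time-preference model.

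**Time outcome.** Section 6.5.1 lists "Mean time to HIV RNA <400 copies/mL" as a secondary outcome. Neither that section nor 6.6.2 says how to score people already below 400 at entry or people who never get there.

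**Sample size.** Section 6.6.3 states: "we anticipate that a minimum of 50% of participants will have HIV RNA <400 copies/mL by six months post-randomization in the control arm". It then claims that about 400 participants give power above 80% for a 15-point difference. Section 4 sets the allocation: "Eligible adults will be randomized in a 1:1 ratio".

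**The concern.** The enrollment value is the primary endpoint's own baseline. Someone below 400 at entry is likely to be below 400 at six months in either arm, while someone who is viraemic still has to link to care, start treatment and suppress. A test that pools the two groups counts the predictable difference between them as noise. The data needed to remove that noise are already collected on everyone.

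For the time outcome, the Protocol itself fixes a mean as the summary. A plain mean has no value for a participant who never reaches the threshold. The simplest workaround, averaging over those who do reach it, conditions on success. An arm that brings in extra, later suppressors can then look slower than an arm that leaves them unsuppressed.

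**Working it through.** **Inputs from the Protocol.** n = 200 per arm (about 400, 1:1); control 50% and incentive 65% (6.6.3); two-sided alpha 0.05; visits at 0, 6, 12, 24 and 48 weeks (6.5.1).

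**Assumed, because the Protocol does not give them.** The share suppressed at entry, s, from 10% to 40%; six-month suppression r = 90% in those people in both arms; the whole 15-point overall effect arising in those unsuppressed at entry.

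**1. The plan's own figure.** Crude variance term: 0.50×0.50 + 0.65×0.35 = 0.4775. Null term with pooled rate 0.575: 2×0.575×0.425 = 0.48875. Power = Φ[(0.15×√200 − 1.96×√0.48875)/√0.4775] = Φ[(2.121 − 1.370)/0.691] = Φ(1.087) = 86%. The continuity-corrected version gives 84%. The stated figure of more than 80% is met.

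**2. Stratifying by enrollment HIV RNA.** Among those unsuppressed at entry, the control rate is c = (0.50 − s×r)/(1 − s) and the incentive rate is i = c + 0.15/(1 − s). The stratified variance term is V = s×2r(1 − r) + (1 − s)×[c(1 − c) + i(1 − i)].

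Example, s = 30%: c = (0.50 − 0.27)/0.70 = 0.329; i = 0.329 + 0.214 = 0.543; V = 0.054 + 0.70×(0.2206 + 0.2482) = 0.382. Ratio to crude: 0.382/0.4775 = 0.80. For power, the null term is 2×[0.3×0.09 + 0.7×0.4357×0.5643] = 0.398, giving Φ[(2.121 − 1.96×√0.398)/√0.382] = Φ(1.43) = 92%.

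| Share suppressed at entry | c | i | V | V / 0.4775 | Variance cut | Power, crude → stratified |
|---|---|---|---|---|---|---|
| 10% | 0.456 | 0.622 | 0.453 | 0.948 | 5% | 86% → 88% |
| 20% | 0.400 | 0.588 | 0.422 | 0.884 | 12% | 86% → 90% |
| 30% | 0.329 | 0.543 | 0.382 | 0.800 | 20% | 86% → 92% |
| 40% | 0.233 | 0.483 | 0.329 | 0.689 | 31% | 86% → 95% |

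With r = 95% the ratios are 0.932, 0.847, 0.737 and 0.592.

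A simulation of the Cochran-Mantel-Haenszel test (40,000 runs per scenario, r = 90%) agrees: 92.1% against 85.8% crude at s = 30%, and 95.3% against 86.1% at s = 40%. Type I error over all simulated scenarios was 4.8–5.1% for both tests.

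**3. Mean time, constructed example on the Protocol's visit grid, 200 per arm.** Numbers first below 400 at 0/6/12/24/48 weeks:
- Control: 60/15/15/10/10, never 90.
- Incentive: 60/15/15/40/10, never 60.

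First below 400 by 24 weeks: 100/200 = 50% vs 130/200 = 65%, so the incentive arm is better.

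| Summary | Control | Incentive | Incentive looks |
|---|---|---|---|
| Mean among achievers, entry-suppressed scored 0 | 990/110 = 9.0 wk | 1710/140 = 12.2 wk | slower |
| Mean among achievers, entry-suppressed left out | 990/50 = 19.8 wk | 1710/80 = 21.4 wk | slower |
| 48-week restricted mean, all 200 | (990 + 90×48)/200 = 26.6 wk | (1710 + 60×48)/200 = 23.0 wk | faster |
| 48-week restricted mean, the 140 not suppressed at entry | 5310/140 = 37.9 wk | 4590/140 = 32.8 wk | faster |

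**The case against.** The strongest reply on the primary analysis is that nothing there is wrong. An unadjusted chi-square on randomised groups holds its error rate and delivers the promised power. Section 6.6.2 leaves room for another suitable method, and covariates are commonly named in an analysis plan, which is not at hand. All of that stands. A reader might infer that the primary result would be biased, that the power statement is wrong, or that the plan rules out adjustment; the Protocol supports none of these.

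Three further readings go too far:
- **A larger gain.** Applying the control rate of 50% to both arms gives variance cuts of 16–43% for shares of 20–40%. At the plan's own alternative of 50% vs 65% the cuts are 12–31%. At a 10% share the gain is only about two power points.
- **Chance imbalance as a separate harm.** Imbalance in baseline suppression is already part of the crude standard error, √(0.4775/200) = 4.9 points. Citing it as well counts the same variance twice.
- **A fault in the randomisation.** Section 6.2 describes blocking only, but nothing shows that the enrollment HIV RNA result is available when participants are allocated. Adjustment in the analysis does not need it by then.

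On the time outcome, Section 6.5.1 does not say that the mean is taken among achievers. People suppressed at entry could be scored as zero, and a restricted mean over everyone points the right way. The example also places the whole benefit at 24 weeks. It shows that a reversal can happen, not that it will. The missing rule for the never-suppressed remains.

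**Conclusion.** The point holds as a gain in precision that needs no new data, together with one secondary outcome to define. The size of the gain depends on a share the Protocol does not report. Under the assumptions above it runs from minor at 10% suppressed at entry (variance down 5%) to material at 30–40% (down 20–31%, equivalent to 1/0.800 − 1 = 25% to 1/0.689 − 1 = 45% more participants). The upper end needs a strong assumption: at 40%, those unsuppressed at entry must move from 23% to 48%.

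The time outcome cannot be computed for never-suppressed participants without a rule. With at least 50% suppression anticipated in control at six months, up to half of that arm could still lack a value then. It is one of three secondary outcomes and does not affect the primary conclusion.

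**What to change.** **Section 6.6.2.** Make the primary estimate a risk difference at six months adjusted for enrollment HIV RNA (below 400 vs 400 copies/mL or more), by Mantel-Haenszel or standardised logistic regression. Keep the unadjusted chi-square as a sensitivity analysis. Naming the adjustment in advance also prevents the open choice of method from being settled after results are seen.

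**Section 6.5.1.** Define the time outcome among participants at 400 copies/mL or more at enrollment. Use either the cumulative proportion first below 400 at each visit, or a restricted mean or interval-censored analysis to 48 weeks. In each case keep never-suppressed participants in the denominator.

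**Cost.** Wording only. The HIV RNA measurements are already scheduled, and neither the sample size, the visits nor the randomisation needs to change.

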### 6.6.3 Sample Size & Accrual

Based on data from our pilot studies in Uganda, we anticipate that a minimum of 50% of participants will have HIV RNA <400 copies/mL by six months post-randomization in the control arm. With a sample size of approximately 400 adults, we have >80% power ( $\alpha=0.05$ , 2-sided) to detect a difference of at least 15% in HIV virologic suppression with the incentive intervention.

## **7. Repeat HIV Testing Incentives – Pilot Trial**

### **7.1 Recruitment & Enrollment of Study Participants**

#### **7.1.1 Recruitment**

Prior to the start of the study, study team members will meet with local officials and community representatives to discuss the study and plans for recruiting individuals at higher-risk of HIV acquisition at social venues. In the selected venues (e.g. trading centers, bars, transport stages), study team members will provide information via pamphlets, flyers or postcards, on local HIV testing venues that potential participants may access. All individuals who subsequently come to the HIV testing venues and undergo an HIV test will be given cash or in-kind compensation of up to \$10 for their time and transport costs. This compensation will be provided to participants upon completion of the HIV testing.

Men and women who come to the testing venue and test HIV negative will be recruited to enroll in the Repeat HIV Testing Incentives – Pilot Trial. Following post-test counseling, study staff will describe the trial and proceed with obtaining written consent for enrollment from those who meet the eligibility criteria below. Persons who wish to consider enrolling in the trial at a later date will remain eligible for screening for enrollment in the Repeat HIV Testing Incentives – Pilot Trial, and receive information on how to contact study staff for enrollment at a later date.

#### **7.1.2 Consent Process**

Study staff will review the informed consent form with recruited adults who meet the inclusion and exclusion criteria below, and answer any questions about study participation. Eligible individuals who provide written consent to study enrollment will be administered a brief questionnaire and fingerprinted before being randomized. Individuals who provide written informed consent and meet criteria for enrollment will proceed to randomization.

#### **7.1.3 Screening for Enrollment**

##### **7.1.3.1 Inclusion Criteria**

- (a) HIV-negative by rapid HIV antibody testing at pilot trial baseline,
- (b) Ages 18 – 59 years old,
- (c) Attendee of high-risk site of HIV acquisition (e.g. bars, trading centers, etc.) in the region

##### **7.1.3.2 Exclusion Criteria**

- (a) Intention to move away from the community in the 3 months from time of recruitment.

#### **7.2 Randomization**

Eligible participants will be randomized to one of three main arms: 1) a standard gain-framed incentive arm in which participants will be offered an incentive for coming for a repeat HIV test in the future; 2) a loss-aversion incentive in which participants will be asked to voluntarily make a deposit that can be retrieved if they come for an HIV test in the future (i.e. for repeat testing); and 3) a no incentive (control) arm in which participants will simply be encouraged to come for a repeat HIV test in the future. Randomization will occur as follows: study staff will provide participants previously block-randomized scratch cards or envelopes to determine which condition each participant receives. Study staff and participants will not know what study condition an individual is randomized to until the participant scratches the card.

#### **7.3 Gain-framed incentive (reward group)**

Study staff will tell participants that they will receive an incentive payment if they come for HIV testing in the near future (within approximately 1-3 months from the time of enrollment). The incentive amount will not exceed US\$10. Participants will be encouraged to come for HIV testing in the future and told that they will receive the payment after undergoing the HIV test.

#### **7.4 Loss-aversion incentive (deposit contract group)**

In the loss aversion arm, study staff will ask participants if they would like to make a deposit of a certain amount, not exceeding US\$10. The amount of compensation given to participants for participating in baseline

HIV testing (as described above in 7.1.1 Recruitment) will facilitate the ability of interested participants to make a deposit. Study staff will retain deposits securely and participants will receive a receipt indicating their deposit amount. Participants will be able to retrieve their deposit when they return for HIV testing in the future. In addition to the deposit, participants will receive interest on their deposit such that the final payment if they return for HIV testing in the future is the same as that in the gain-framed incentive arm. The possibility that participants will lose their deposit if they do not come for an HIV test within specific testing periods (e.g. 1, 3 months) will be communicated clearly by study staff; deposits from individuals who do not test will be retained by the study team and will be used for other study-specific activities. This aspect of deposit contracts is essential in order for the principle of loss aversion to have an impact on participants' HIV testing behavior.

Study staff will also emphasize the voluntary nature of the deposit contract and remind participants that they are not required to make a deposit. Participants who decline to provide a deposit at baseline will still be encouraged to come for an HIV test within a specific testing period (e.g. 1,3 months), but will not receive any incentive for the return HIV test.

We will consider having multiple sub-groups in which participants are asked to make deposits ranging from 25%-50% of the compensation amount provided for baseline testing (see 7.1.1 Recruitment, above); the goal being to learn what amount of deposit is most feasible for participants.

Incentives of this form are sometimes referred to as deposit contracts or commitment contracts, and they apply the principle of loss aversion to help motivate participants who are committed to going for repeat HIV testing to follow through on their commitment. Such types of incentives have previously been implemented in various settings including Kenya, Thailand, and the United States [57-59].

